### Data plan and analysis

Recruitment, retention and trial completion data will be visually represented in a CONSORT diagram. Quantitative outcome analysis, encompassing measures such as IES-R, CAPS-5, PHQ-9, GAD-7 and EQ5D-5L, will primarily be descriptive, emphasising estimation. Baseline measures and outcomes will be summarised using appropriate descriptive statistics, complete with associated CIs. The focus of interpretation will centre on the implications of these results for the feasibility of the main trial. Furthermore, we will conduct a confirmatory factor analysis of the DSM-5’s four-factor PTSD diagnostic criteria, utilising data pooled from the CAPS-5 interviews.

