### 12-month follow-up assessment

Research staff will ask all participants, in both the observation group (part A only) and RCT (part A and part B), to repeat the IES-R, PHQ-9, GAD-7 and the EQ-5D-5L, at 12 months posthospital discharge. See table 1 for the full study schedule of events.

**Table 1 T1:** EMERALD study schedule of events

	Baseline	2 months postdischarge	3–9 months postdischarge	12 months postdischarge
Informed consent	X Part A	X* Part B		
Demographics	X			
IES-R	X	X		X
CAPS-5, CGI-S*		X*		X*
PHQ-9	X	X		X
GAD-7	X	X		X
EQ-5D-5L	X	X		X
EMDR intervention			X*	
IES-R, PHQ-9, GAD-7 (EMDR group only)				
Randomisation preference*		X*		
Process evaluation			X	X

X* for participants consenting to part B of the study only.

CAPS-5, Clinician Administered PTSD Scale for DSM-5; CGI-S, Clinical Global Impression of Illness Severity; EMDR, eye-movement desensitisation and reprocessing; EQ-5D-5L, EuroQol-5 Dimensions-5 Levels; GAD-7, Generalised Anxiety Disorder 7; IES-R, Impact of Events Scale-Revised; PHQ-9, Patient Health Questionnaire-9; PTSD, post-traumatic stress disorder; QoL, quality of life; RCT, randomised controlled trial.

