### Part B participant recruitment

Participants scoring≥22 on the 2 month IES-R will receive a phone call or email from the study team, inviting them to consider consenting to part B, the EMDR versus usual care RCT. The part B PIS and ICF will be accessible electronically or via postal delivery. Those who consent to part B will first undergo a Clinician Administered PTSD Scale for Diagnostic and Statistical Manual of Mental Disorders, fifth edition (CAPS-5) assessment to evaluate PTSD symptoms and a Clinical Global Impression of Illness Severity (CGI-S) assessment with the Chief Investigator (CI). Additionally, participants will be asked to rate their preference for study arm strength using a Likert scale ranging from 0 to 10.

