### Sample size

As this is a feasibility study, an a priori sample size calculation is not applicable. The findings will guide the sample size determination for a potential definitive RCT. Sample sizes of feasibility studies between 24 and 50 have been recommended to provide adequate estimate of SD for sample size calculation.^39 40^

To achieve this, a total of 160 patients will be enrolled in part A to assess feasibility adequately. Based on an expected incidence of 20%–25% post-ICU PTSD, we anticipate that around 40 patients will proceed to the part B RCT with an IES-R PTSD score≥22. The remaining 120 participants will continue in the observation arm, with a 12 month reassessment. Accounting for an estimated 25% mortality or loss to follow-up across all study arms, we anticipate approximately 30 participants completing the RCT and 90 participants completing the observation arm.

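### The planned four-factor CFA rests on CAPS-5 data from only about 40 selected Part B participants, too few to confirm or refute the factor structure

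*Protocol article*

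**What the plan says.** The protocol article, under Data plan and analysis, describes the quantitative work as mainly descriptive and then adds one model-based analysis: "we will conduct a confirmatory factor analysis of the DSM-5’s four-factor PTSD diagnostic criteria", "utilising data pooled from the CAPS-5 interviews". It does not say whether pooling is over sites, arms, visits or several of these.

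Table 1 (12-month follow-up assessment) schedules CAPS-5 at 2 and 12 months and flags both entries with the mark explained as "X* for participants consenting to part B of the study only". Part B participant recruitment agrees: "Those who consent to part B will first undergo a Clinician Administered PTSD Scale". Entry to Part B depends on a symptom threshold: "Participants scoring≥22 on the 2 month IES-R will receive a phone call or email from the study team". The observation arm has no CAPS-5, and no other source of CAPS-5 data is described.

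Under Sample size, "a total of 160 patients will be enrolled in part A to assess feasibility adequately". "Based on an expected incidence of 20%–25% post-ICU PTSD", about 40 are expected in Part B, and after 25% attrition "we anticipate approximately 30 participants completing the RCT". The size is justified only by a recommended range of 24 to 50 for estimating a standard deviation.

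**The concern.** A confirmatory factor analysis compares an observed covariance matrix with the one implied by a prespecified model. It needs enough independent people for the covariances to be stable and for the fit statistic to follow its reference distribution. Here the sample was sized for a standard deviation, while a correlated four-factor model has dozens of parameters.

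Three features add to the small number. Everyone was selected on a score for closely related symptoms, which restricts the range of the variables being modelled. If visits are pooled, the same person contributes two records. Some of those second records follow EMDR and others do not.

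At stake is a secondary claim. A poor fit could be published as evidence that the DSM-5 structure does not hold in ICU survivors when it only reflects sample size. An acceptable fit would be equally weak support.

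**Working it through.** **1. The plan's own numbers.** Part B: 160 × 0.25 = 40, which reproduces the stated figure at the top of the incidence range; 160 × 0.20 = 32 at the bottom. Both assume that everyone above threshold consents, although the protocol provides for people who decline. Completers: 40 × (1 − 0.25) = 30, as stated.

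**2. Interviews if visits are pooled.** 40 + 30 = 70 interviews from about 40 people. The 2-month CAPS-5 precedes randomisation, and allocation is 1:1, so interviews after EMDR number about 30 × 1/2 = 15, or 15/70 = 21%.

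**3. Parameters.** With p items and four correlated factors: p loadings + p residual variances + 4 × 3/2 = 6 factor correlations, that is 2p + 6. Distinct moments are p(p + 1)/2. The item count is not in the document, so it is varied.

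| Items (assumed) | Free parameters | Degrees of freedom | People per parameter, n=40 |
|---|---|---|---|
| 20 | 46 | 210 − 46 = 164 | 0.87 |
| 16 | 38 | 136 − 38 = 98 | 1.05 |
| 12 | 30 | 78 − 30 = 48 | 1.33 |

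**4. Simulation of a correct model.** Data were generated from the four-factor model itself and fitted by maximum likelihood, with T = (N − 1)F tested against chi-square at 5%. Assumptions not in the document: 20 items split 5/2/7/6, loadings 0.7, factor correlations 0.7, normal data and no selection, unless stated otherwise. There were 350 to 1,500 replicates per row.

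| n (independent people) | Rejected, uncorrected | Rejected, Bartlett | Improper or boundary solution |
|---|---|---|---|
| 30 | 96% | 1% | 28% |
| 32 | 93% | 2% | 23% |
| 40 | 79% | 3% | 15.5% |
| 70 | 37% | 3.5% | 3% |
| 100 | 21% | 4% | 1% |
| 200 | 14% | 4% | 0% |
| 500 | 8% | 6% | 0% |

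At n=40 in this setting, RMSEA exceeded 0.06 in 88% of samples and CFI fell below 0.95 in 92%, so the common fit indices fail too.

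**5. Sensitivity with 40 people.**

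| Setting | Rejected, uncorrected | Rejected, Bartlett | Improper |
|---|---|---|---|
| 20 items, loadings 0.5, correlations 0.5 | 77% | 3% | 60% |
| 20 items, loadings 0.6, correlations 0.8 | 77% | 3% | 57% |
| 20 items, loadings 0.8, correlations 0.5 | 80% | 3% | 15% |
| 20 items, loadings 0.8, correlations 0.8 | 79% | 3% | 6% |
| 20 five-category items treated as continuous | 89% | 7% | 29% |
| 16 items | 46% | 1% | 9% |
| 12 items | 23% | 3% | 26% |
| 40 + 30 interviews, same people, treated as independent (assumed within-person correlation 0.5) | 92% | 43% | 6% |

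Further runs of the 20-item model at n=40 gave 81–83% uncorrected rejection and improper solutions in 14% to about 65%. Pooling visits does not buy the n=70 result: that row needs 70 different people, and with repeat records even the Bartlett-corrected test rejects a true model in 43% of samples.

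**The case against.** The protocol names no item count, estimator or fit test, and such details may properly sit in an analysis plan that is not shown. A reader might infer that the fit test will reject a correct model most of the time. The document does not support that without conditions: the figure needs about 20 items and an uncorrected test, and a standard small-sample correction brings rejection close to or below the nominal 5%. This objection stands, and the rates above must be read as conditional.

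Two other strong readings also fail. One is that parameters outnumber people whatever the item count; with 12 items, 40 people exceed 30 parameters. The other is that half of the pooled interviews follow EMDR; half is right for the 12-month interviews alone, and about 15 of 70 for the pool.

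Pooling may mean pooling over sites and arms at one visit, in which case dependence does not arise; but then n is 40 at most. The effect of selection on IES-R was not simulated and is a qualitative point only. It is also fair that the article stresses description, and that how the authors would interpret a misfit is not known.

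The objection does not reach the sample itself. The article fixes who has CAPS-5 and roughly how many they are, and no estimator adds people. A corrected test controls false rejection for independent records; it does not remove improper solutions or show that 40 people could detect a wrong structure, which was not examined here.

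**Conclusion.** The concern holds in a limited form. The protocol commits to a confirmatory analysis on about 40 selected people (32 or fewer is plausible), and at that size the result cannot be relied on to confirm or refute a four-factor structure.

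Assuming 20 items, there are 46 parameters for 40 people. The uncorrected test falsely rejects in about 80% of samples, falling to about 46% with 16 items, 23% with 12, and about 1–3% with a Bartlett correction on independent normal data. Improper solutions occur in about 15–65% of samples in most 20-item settings, with 6% in the most favourable one tried, whichever test is used. Pooling over visits adds dependence, not people.

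The analysis is ancillary. It is absent from the stated objectives and from the listed primary and secondary outcomes, so feasibility, acceptability and the variance estimates for the definitive trial are not affected.

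**What to change.** Remove the CFA from this study. In its place report CAPS-5 item and symptom-cluster distributions and internal consistency, with 95% confidence intervals, from the 2-month interview before randomisation, so that each person contributes one record. Keep the item-level data for a CFA in the definitive trial or a larger pooled dataset.

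If the CFA is kept, label it exploratory, state what is pooled and the number of people, use one record per person and a small-sample-corrected test, and say that no conclusion about PTSD structure will be drawn from its fit.

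The cost is a change to one sentence and one ancillary analysis lost or downgraded. The replacement fits the descriptive, estimation-based approach that the same section already sets out.

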### Qualitative process evaluation

Qualitative description will be employed to construct a comprehensive overview of participants’ and staff perceived experiences and the impact of the EMERALD study. This includes assessing the perceived burden associated with study participation and undertaking research activities. Qualitative interview data will serve to validate, elaborate on and broaden our understanding of the study’s acceptability and feasibility, while also shedding light on potential factors that may hinder or enhance the EMERALD study. This information will be invaluable in refining the design of the subsequent RCT.

### Method for obtaining and evaluating qualitative data

The process evaluation aligns with MRC guidance for complex intervention evaluations.^41^ To efficiently capture implementation processes, we will employ Rapid Assessment Procedure Informed Clinical Ethnography.^42^

*Stage 1: data collection* involves selecting a purposive, diverse sample of trial participants and psychological therapists, minimising bias by adapting the sample to study needs. Participants will be invited for recorded telephone or videoconference interviews at their convenience. We will use semistructured interviews guided by relevant objectives, incorporating patient and public involvement (PPI) recommendations, recent literature and a systematic review. See online supplemental material 4 for participant interview guide and psychological therapist interview guide. Sampling will continue until data saturation is reached, typically with 15–20 interviews.^43^ The questions will be open-ended, and we will take field notes while digitally recording and transcribing interviews. The data will be reviewed by a senior researcher within the team to assess the need for further data collection.

10.1136/bmjopen-2023-081969.supp4Supplementary data

*Stage 2*: the anonymised data set will be securely stored and analysed using NVivo qualitative data software. The analysis will follow the theoretical framework of acceptability, deductively coding content into seven constructs;^32^ affective attitude, burden, intervention coherence, ethicality, opportunity costs, perceived effectiveness and self-efficacy.

Preliminary interpretation of emerging themes will be independently conducted, with consensus reached through discussion. Additional data collection will be considered if necessary. Agreed findings will be presented to a sample of study participants and PPI representatives to ensure validity and comprehensiveness.

*Stage 3*: will integrate qualitative findings with quantitative RCT data during the post-study interpretation phase. We will map data using a mixed-methods joint display,^44^ and providing a holistic understanding of predetermined study objectives following established principles.

### Safety considerations

Several systematic reviews have reported no adverse events attributable to EMDR. The intervention will be undertaken by suitably trained and experienced psychological therapists employed by the NHS. The service has an established and defined risk management and clinical governance structure. Online sessions will be compliant with Digital Approaches to therapy guidance from the British Psychological Society and NHS Digital. (This guidance contains expected standards relating to safeguarding, information governance, and GDPR.)

Participants who exhibit symptoms of intrusion/escalation will be treated according to the protocol unless it is determined that further treatment or escalation to emergency care may be necessary/indicated. If further treatment is required, the most appropriate course of action and referral pathway will be decided on a case-by-case basis by the psychology team. If deemed necessary, the CI will be unblinded to group allocation, to contribute to the safety discussion.

### Monitoring and trial oversight

Day-to-day management will be the joint responsibility of the CI, Senior Project Co-Ordinator and Co-Investigators. This project is part of a PhD study undertaken by [name] (CI) with supervision by the co-investigators and authors.

#### Monitoring

The CI will facilitate monitoring by the local quality manager, REC review and provide access to source data as required. Following any monitoring, a report will be provided which will summarise the visit and documents, along with any fi/ndings. The CI will be responsible for ensuring that all findings are addressed appropriately. The study group will review all events in a timely manner. Additional monitoring will be scheduled where there is evidence of suspicion of non-compliance with the study protocol.

### Patient and public involvement

PPI has shaped the study design, and this collaboration will persist throughout the project in the following ways:

#### Patient advisory group

An established PPI group attended advisory group meetings during project development. We are planning for meetings to occur every 6 months to review research findings, discuss key points, review press releases and dissemination outputs. Any study design amendments will be discussed and approved before submission.

#### Study management steering group

Two PPI members will serve as patient representatives in this decision-making group. They will oversee trial progress, review findings and outputs, approve project changes, and address arising issues, conflicts and risks in three meetings per year. One PPI group member will attend an intensive care conference to copresent study findings to clinical and academic leaders.

#### Patient groups and third sector

Study findings and dissemination outputs will be shared with and reviewed by patient groups and organisations such as ICU steps, EMDR UK, EMDR Europe and Anxiety UK. This ensures the inclusion of the patient perspective in the manuscript and keeps relevant stakeholders well informed.

Meetings will be conducted face-to-face with the option of videoconferencing for accessibility. A plain English research report, agenda and previous minutes will be circulated before each meeting, and meetings may be recorded with participant consent for later reference. Ongoing training tailored to individual needs will be provided for all participants, and the Public Involvement Lead for South Central Research Design Service will oversee ongoing PPI efforts.

## Ethics and dissemin§ation

This study obtained prior approval from the South Central -Hampshire A Research Ethics Committee (REC) (22/SC/0410) before approaching participants, who will also review protocol modifications. Ethics approval covers all NHS trial sites, which were activated before enrolling patients.

The trial will adhere to the principles outlined in the 18th World Medical Assembly’s recommendations from Helsinki 1964, as revised and recognised by governing laws and EU Directives. Consent to participate in the trial will be obtained only after providing a comprehensive explanation of treatment options, including conventional and widely accepted methods. The right of individuals to decline participation without specifying reasons will be respected.

Once a participant is enrolled in the trial, clinicians may administer alternative treatments beyond the protocol if they deem it in the participant’s best interest, with the reasons duly documented. The participant will continue within the trial for follow-up and data analysis based on their allocated treatment option. Likewise, participants are free to withdraw from protocol treatment and trial follow-up at any time without providing reasons, without affecting their subsequent treatment.

The CI will inform the REC on study completion. In cases of premature termination, the CI will promptly notify the REC, including the reasons for the early conclusion.

Within 1 year following the study’s conclusion, the CI will submit a final report containing results and any related publications or abstracts to the REC.

Dissemination activities will include but not be limited to:

Publication in peer reviewed journals.Feedback to PPI study focus group.Feedback to study participants.Presentations to local clinical teams and managers and commissioners.Presentation at international conferences and within inter-disciplinary clinical networks.Public webinars, digital and social media.

## Discussion

The EMERALD study represents the second phase of our innovative exploration into whether EMDR can alleviate psychological distress after ICU discharge. Our mixed-methods approach, in line with MRC guidance for assessing complex healthcare interventions, enhances the study’s robustness.^41^ It allows us to capture cultural and contextual factors often missed in purely quantitative designs, thus improving the reliability of our findings and informing the design of our upcoming definitive RCT.

Building on the lessons from our prior study, CovEMERALD,^28^ we have incorporated screening for psychological distress before entry into the RCT, aligning with recent review recommendations.^45^ Adopting a 2 months posthospital discharge screening for PTSD follows both ICU rehabilitation^46^ and PTSD treatment guidelines.^24^ Furthermore, participants have the flexibility to choose either face-to-face or online intervention, without challenging participants’ physical or psychological vulnerabilities.

A noteworthy aspect of this project is the strong collaboration between clinical academics specialising in intensive care, psychiatry and psychology, bolstered by our patient representatives, individuals with valuable lived experiences.

It is important to interpret clinical findings from this study cautiously, as it is not powered to detect clinically significant differences between groups. Nevertheless, these outcomes will inform future power calculations for the definitive RCT.
